#### R3 antimicrobial prophylaxis

Children will be randomly allocated on a 1:1 basis to receive either receive: (i) cotrimoxazole prophylaxis for 3 months post discharge or (ii) no antibiotic prophylaxis post discharge (control, SOC). Cotrimoxazole dispersible tablets (240 mg: trimethoprim 40 mg/sulphamethoxazole 200 mg) will be used and dosing will follow WHO recommendations for prophylaxis in HIV-infected children: age 2 to 6 months: 120 mg; age 6 months to 5 years: 240 mg; children > 5 years: 480 mg [38]. The dispersible tablets may be taken with water or mixed with feeds. Cotrimoxazole will be prescribed from discharge (or 5 days from randomisation in those not discharged by this timepoint). The cotrimoxazole prophylaxis randomisation will be pragmatic in that all children for whom cotrimoxazole prophylaxis should be prescribed according to WHO or national guidelines (e.g. HIV-infected children) will receive it regardless of randomisation, and no child in whom it is contraindicated (e.g. known GP6D deficiency according to local testing) will receive it. Such children will essentially ignore their allocated cotrimoxazole randomisation; any cotrimoxazole received per guidelines would be recorded on study CRFs. The number of children with these conditions is expected to be small (< 5 %). HIV-infected children will receive antiretrovirals and will continue in the trial with HIV management and follow-up tailored in collaboration with local HIV clinics.

### Co-enrolment guidelines

Patients will not ordinarily be permitted to participate in any other clinical intervention trial or research protocol while on the TRACT trial. Participation in other studies that do not involve an intervention may be acceptable, following agreement from the TRACT trial management group (TMG). The TRACT TMG will consider co-enrolment of TRACT participants onto other trials where the interventions do not conflict with the TRACT objectives on a case-by-case basis.

### Measurement of endpoints

#### Assessment during hospital

The clinicians will complete a detailed clinical review on the CRF and perform a physical examination at enrolment. A symptom checklist and targeted physical examination will be performed at each subsequent clinical assessment. Children will be intensively monitored on the day of admission by the clinical team, and during any transfusion and then reviewed daily by the study team until discharge, with Hb testing performed at least 8 hourly in the first 24 hours, and daily thereafter. At each review conscious level, vital signs (heart rate, oxygen saturation, respiratory rate, axillary temperature, blood pressure) will be recorded, and examinations will specifically review the child for solicited adverse events. The doctor will be responsible for documenting and reporting serious adverse events (SAEs). Admission and final diagnoses will be recorded in the CRF.

### Follow-up

A symptom checklist and targeted physical examination will be performed at each clinic visit post discharge. Medical history since last visit including hospital re-admissions, transfusions, specific solicited adverse events, and grade 3 or 4 adverse events related to nutritional and antibiotic interventions will be documented by a doctor, including severity and likely relationship of any adverse events to trial interventions. At Day 28 adherence to and acceptability of MVMM and/or cotrimoxazole will be queried by carer self-report, and carers will be provided with a supply of drugs sufficient to last for the next 2 months (Day 90 since admission). Blood and other tests and sample storage will require a maximum of 4 mls heparinised blood (plasma) and 1 ml into ethylenediaminetetraacetic acid (EDTA) (for pathogen diagnostics). At Day 90, adherence/acceptability will again be recorded, but no more supplements/antibiotics will be given. Any participants requiring further care at their Day 180 visit will transferred into the routine clinics at the centre where the trial is being conducted. Locator maps and contact numbers will be obtained to facilitate follow-up.

### Withdrawing from the trial and protocol treatment discontinuation

In consenting to the trial, parents or guardians and children are consenting to trial treatment, data collection and follow-up. If a patient chooses to discontinue any part of their trial treatment, they should always be encouraged not leave the whole trial and to return for follow-up, providing they are willing. After the participant has entered the trial the clinician remains free to give alternative treatment to that specified in the protocol at any stage if he/she feels it is in the participant’s best interest, but the reasons for doing so should be recorded. In these cases the participants remain within the study for the purposes of follow-up and data analysis. All carers and participants are free to withdraw at any time from the protocol treatment without giving reasons and without prejudicing further treatment. If they do not wish to remain on trial follow-up, however, their decision will be respected and the patient will be withdrawn from the trial completely.

Withdrawal from the transfusion intervention or control arms is unlikely, given that most transfusions are given within the first 12 hours of admission. Severe allergic reaction (toxicity) or Transfusion Related Acute Lung Injury (TRALI) is included as a secondary endpoint and is relevant only to children receiving transfusion. It will not be a reason to withdraw the child from the trial, but further transfusions should be withheld. The child should continue with their cotrimoxazole/MVMM allocation wherever possible.

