### Study design and population

TRACT is a multicentre randomised controlled trial of 3954 children aged 2 months to 12 years admitted to hospital with a Hb < 6 g/dl. Children will be enrolled over 2 years from 2 countries and followed for 6 months. The trial will simultaneously evaluate 3 ways to reduce short-term and longer-term mortality (primary endpoint) and morbidity following admission to hospital with SA in sub-Saharan Africa using a 3 x 2 x 2 factorial design. All randomisations will be open. Inclusion/exclusion criteria are detailed in Table 1.

**Table 1 Tab1:** Inclusion and exclusion criteria

Inclusion criteria	Exclusion criteria
Aged 2 months to 12 years	Malignancy or other terminal illness
Severe anaemia (Hb < 6 g/dl) on the day of admission to hospital	Acute trauma or burns as main reason for admission
Care-giver willing/able to provide consent	Surgery as main reason for admission
	Chronic renal or liver failure
	Signs of bi-ventricular heart failure
	Known congenital or valvular heart disease (non-surgically corrected)
	Children who are exclusively breast fed (thus unable to take nutritional support)

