### Outcomes

Primary outcome and secondary outcomes are detailed in Table 3. The methods for assessing efficacy include:

**Table 3 Tab3:** Outcome measures

Primary outcome
Cumulative mortality to 28 days for the transfusion strategy comparison, and to 180 days for the nutritional support/antibiotic prophylaxis comparison
Secondary outcomes
Mortality: at 48 hours, 28 days, 90 days and 180 days (cumulative) where not the primary outcome
Morbidity: endpoints relating to the specific mechanisms of action of each intervention:
re-admission to hospital
haematological:
proportion achieving correction of anaemia (defined by the WHO as Hb > 9 g/dl) at 48 hours, 28 days, 90 days and 180 days
development of new profound anaemia (Hb < 4 g/dl) during acute admission or development of severe anaemia (Hb < 6 g/dl) post discharge
nutritional: changes in weight and mid-upper arm circumference (MUAC) at 90 days and 180 days
anti-infection: changes in inflammatory markers (C-reactive protein (CRP) , procalcitonin), incidence of bacterial infections and malaria at 28 days, 90 days and 180 days
solicited adverse events: suspected transfusion reactions: febrile reactions, TRALI (Transfusion Related Acute Lung Injury) (any grade); grade 3–4 toxicity of cotrimoxazole, MVMM or standard iron/folate
serious adverse events
costs and cost-effectiveness

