#### Clinical events

Survival status will be recorded at discharge and each subsequent visit (28 days, 90 days and 180 days following admission). Any patient lost to follow-up before 6 months without withdrawing consent will be traced for vital status. Other SAEs will be reported as and when the doctor becomes aware of them. The details reported will include bedside observations, laboratory data, and additional clinical narrative. During the index admission, any child fulfilling criteria for a new or additional transfusion will be recorded. At all subsequent visits hospital admissions and requirement for transfusion will be solicited.

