### Methods of reducing bias

Protection against bias is principally provided by a completely objective primary endpoint (mortality). Any child lost to follow-up before 6 months will be traced for vital status. Cause of death (and other clinical secondary endpoints) will be adjudicated by an Endpoint Review Committee (ERC), blinded to randomised allocations. The ERC will adjudicate on causes of death and whether fatal and non-fatal SAEs were unlikely, possibly/probably or uncertainly related to each of the randomised interventions (transfusion volume, MVMM, cotrimoxazole), if the child were to be receiving them (without knowledge of actual randomisation), to protect from bias in this open trial. The randomisations to transfusion strategies and long-term support are open because of logistical constraints – it is impossible to blind transfusion or nutritional strategies since MVMM is in a sachet and iron and folate are largely provided separately as a syrup and crushable tablets or tablets alone. Whilst cotrimoxazole prophylaxis could be blinded, the intention of this pragmatic strategy trial is to also assess likely impacts of non-compliance to taking cotrimoxazole on an antibiotic prophylaxis strategy in SA.

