### Statistical analysis

The analyses will be described in detail in a full Statistical Analysis Plan. In brief, each intervention is hypothesised to be superior to SOC and, therefore, the proposed analysis is intention-to-treat, including all randomised patients. The primary analysis will compare: a) transfusion versus no transfusion (strata b only) and b) 20 ml/kg versus 30 ml/kg (strata a and b) in terms of the proportion of children with fatal outcome 28 days after randomisation. Primary outcome analysis will use time-to-event methods (Kaplan-Meier, log-rank test, proportional hazards models) to the timepoints specified for primary and secondary outcomes, stratified by centre and anaemia severity at baseline. Correction of anaemia will also be analysed using time-to-event methods.

Pre-specified subgroup analyses will include each of the other randomised allocations (ie exploration of interactions in the factorial design), together with the other randomisation stratification factor (centre) and the anaemia stratification factor (a versus b) for the transfusion randomisation. We will also investigate a priori whether there was any evidence for a different impact of the interventions according to the following categorical variables: previous receipt of a transfusion (ever or at another health centre in this illness); speed (rate) at which the transfusion is administered; fever; malaria; microbiological evidence of sepsis (blood culture or retrospective molecular diagnosis); HIV; known or previously undiagnosed sickle cell disease.

For the cotrimoxazole prophylaxis and MVMM supplementation randomisations the primary analysis will be intention-to-treat based on all randomised participants, as above. However, secondary analyses will be restricted to: (i) patients discharged alive, and (ii) patients discharged alive in whom these interventions were neither mandated nor contraindicated (ie excluding HIV-infected children and those with known GP6D deficiency from the cotrimoxazole randomisation, and excluding children admitted for severe acute malnutrition from the supplementation randomisation).

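### Complete withdrawal leaves no route to vital status alone, so the primary outcome may be lost for these children, and the bias section omits this exception (minor)

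*Protocol article*

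**What the plan says.** Three sections of the protocol article bear on this.

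- **Withdrawing from the trial and protocol treatment discontinuation** describes two levels. Families who stop trial treatment stay in the study if they will: "they should always be encouraged not leave the whole trial and to return for follow-up, providing they are willing". If they do not want to remain on follow-up, "their decision will be respected and the patient will be withdrawn from the trial completely". No level between these is described. The same section expects withdrawal from the transfusion intervention or control arms to be unlikely, because most transfusions are given in the first 12 hours.
- **Clinical events** gives the tracing rule with its limit: "Any patient lost to follow-up before 6 months without withdrawing consent will be traced for vital status".
- **Methods of reducing bias** gives the same rule with no limit: "Any child lost to follow-up before 6 months will be traced for vital status". This comes directly after the statement that an objective mortality endpoint is the main protection against bias.

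The context is as follows. Under Study design and population, "All randomisations will be open". The primary outcome in Table 3 is "Cumulative mortality to 28 days for the transfusion strategy comparison, and to 180 days for the nutritional support/antibiotic prophylaxis comparison". Under Statistical analysis, "the proposed analysis is intention-to-treat, including all randomised patients", with time-to-event methods for the primary outcome. The Follow-up section says that locator maps and contact numbers will be obtained.

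**The concern.** An objective endpoint protects against biased assessment only where it is obtained. A carer who declines further follow-up may have no objection to one call or home contact to learn whether the child is alive, but the withdrawal section does not provide for asking. That child's later vital status then goes unrecorded, and the child is censored in a time-to-event analysis. Censoring is harmless if withdrawn children go on to die at the same rate as those still followed in their arm.

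Families know the allocation, so reasons for leaving could differ by arm. The supplement and cotrimoxazole comparisons ask for three months of treatment and visits at days 28, 90 and 180, which leaves more time and more occasion to withdraw than the 28-day transfusion comparisons do. An analysis plan can choose how to handle missing vital status, but it cannot recover a status that nobody had permission to collect.

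The bias section's unqualified wording would also let a reader believe that the safeguard covers every child.

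**Working it through.** **1. The sections side by side**

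| Situation | Withdrawal section | Clinical events | Bias section |
|---|---|---|---|
| Stops treatment, stays in follow-up | Encouraged to return | Status recorded at visits | Not at issue |
| Stops attending, consent not withdrawn | Not addressed | Traced | Traced |
| Actively declines follow-up | Completely withdrawn | Not traced, if this counts as withdrawing consent | Traced, if read literally |

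Only the third row is open. The gap between Clinical events and the bias section is one missing qualifier.

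**2. The plan's loss allowance**

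3730 × 1.06 = 3953.8, which reproduces 3954. The 6 % (0.06 × 3954 = about 237 children) covers all loss by 6 months. The protocol gives no separate figure for complete withdrawal and no split by arm. The allowance is therefore an upper reference, not an estimate of withdrawals.

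**3. How large a bias could be**

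Two inputs are assumptions that are not in the documents: *w*, the share of an arm that withdraws completely, and *r*, the mortality of those children as a multiple of the arm's true mortality *p*, with all their deaths unseen.

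- Observed mortality = *p*(1 − *wr*)/(1 − *w*)
- Bias = *p* × *w*(*r* − 1)/(1 − *w*)

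With *r* = 1 the bias is zero for any *w*. The multiplier *w*(*r* − 1)/(1 − *w*) is 0.01/0.99 = 0.0101 for *w* = 1 %, *r* = 2; 0.04/0.98 = 0.0408 for *w* = 2 %, *r* = 3; and 0.12/0.94 = 0.1277 for *w* = 6 %, *r* = 3.

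For the supplement and cotrimoxazole comparisons the protocol gives no clean 6-month mortality for planning. Its 25 % is labelled mortality, but it adds 12.5 % for re-admission, relapse and re-transfusion to 4-week mortality (9 + 12.5 = 21.5; 16 + 12.5 = 28.5). The 4-week mortality alone averages 0.5 × 9 + 0.5 × 16 = 12.5 %. Both values are shown as a range. Withdrawal is placed in the control arm only:

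| *w*, *r* | Bias, *p* = 12.5 % | Bias, *p* = 25 % | Share of the 5-point target |
|---|---|---|---|
| 1 %, 2 | 0.13 points | 0.25 points | 3 % to 5 % |
| 2 %, 3 | 0.51 points | 1.02 points | 10 % to 20 % |
| 6 %, 3 | 1.60 points | 3.19 points | 32 % to 64 % |

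The last row puts the whole loss allowance into complete withdrawal, so it is an extreme and not an expectation.

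For 20 versus 30 ml/kg (13.67 % versus 9.57 %, a 4.10-point effect), the same three cases in the 20 ml/kg arm only give observed mortality of 13.53 %, 13.11 % and 11.92 %. The bias is 0.14, 0.56 and 1.75 points, or 3 %, 14 % and 43 % of the effect. With equal *w* and *r* in both arms, the 4.10-point difference becomes 4.06, 3.93 and 3.58.

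**4. Why these figures run high**

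A child who withdraws is alive at that moment, and earlier deaths are counted. On the plan's inputs, 5 points of mortality fall between 48 hours and 4 weeks in each stratum (16 − 11 and 9 − 4). If withdrawal happens at 48 hours and *r* applies to the remaining risk, the 4-week bias for *w* = 2 %, *r* = 3 is 5 × 0.0408 = 0.20 points. Applying *r* to the full 9 % gives 9 × 0.0408 = 0.37 points.

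**5. Direction**

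Unseen deaths in the control arm shrink an apparent benefit. In the intervention arm they would enlarge it. The documents do not indicate which would apply.

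**The case against.** A reader might infer that mortality *is* lost selectively. The documents do not support that. Selective loss needs withdrawal to be related to both arm and risk of death, and no section gives a withdrawal rate, a split by arm or a link to prognosis. For the transfusion arms the protocol expects withdrawal to be unlikely. That remark concerns withdrawal from the transfusion intervention or control arms and does not speak to leaving the 6-month follow-up, but it is a fair reason to place the concern mainly on the supplement and cotrimoxazole comparisons.

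Three other strong readings also fail.

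- Refusing only a visit or a blood draw is not declared to be complete withdrawal. The rule applies to carers who do not want to remain on follow-up, and those who merely stop attending are traced.
- The 6 % loss allowance should not be set against the 4.5- and 4.1-point transfusion effects. It covers all loss by 6 months, while those effects are at 4 weeks.
- The difference between the two tracing statements is a weak contradiction. Lost to follow-up is commonly kept distinct from withdrawn consent, and the exception is stated openly under Clinical events.

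It can also be said that levels of withdrawal belong in the full protocol, consent sheet or operating procedures, and the handling of censored children in the analysis plan, none of which is shown. This stands for the analysis. It does not fully answer the point, because the article states the withdrawal rule itself as two levels. Respecting a refusal is proper, and nothing here proposes tracing a child against the carer's wish.

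**Conclusion.** The point holds as a minor one. As written, a carer's decision to leave follow-up ends all knowledge of the child's vital status, which is the whole primary outcome in an open trial, and the bias section describes the safeguard more broadly than the other two sections allow. The size of any bias cannot be determined from the documents. It is nil if withdrawn children die at the same rate as the rest of their arm. On the assumed inputs it is small at 1 % withdrawal with doubled mortality, and material only if withdrawal is both prognostic and unequal between arms or takes up much of the loss allowance. The sample size of 3954 is unaffected.

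**What to change.** - **Withdrawal section:** before complete withdrawal, ask the carer whether vital status alone may still be obtained at day 28 and day 180, and record the answer. Withdraw completely only those who refuse this.
- **Methods of reducing bias:** add the consent exception already stated under Clinical events, so that the two sections match.
- **Reporting:** give complete withdrawals by arm and timing, so that readers can judge whether loss was balanced.

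The cost is one more question at withdrawal, one form field, an ethics notification, and a few phone or home contacts using details the sites already plan to hold. Enrolment numbers and the planned analysis do not change.

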### Outcomes

Primary outcome and secondary outcomes are detailed in Table 3. The methods for assessing efficacy include:

**Table 3 Tab3:** Outcome measures

Primary outcome
Cumulative mortality to 28 days for the transfusion strategy comparison, and to 180 days for the nutritional support/antibiotic prophylaxis comparison
Secondary outcomes
Mortality: at 48 hours, 28 days, 90 days and 180 days (cumulative) where not the primary outcome
Morbidity: endpoints relating to the specific mechanisms of action of each intervention:
re-admission to hospital
haematological:
proportion achieving correction of anaemia (defined by the WHO as Hb > 9 g/dl) at 48 hours, 28 days, 90 days and 180 days
development of new profound anaemia (Hb < 4 g/dl) during acute admission or development of severe anaemia (Hb < 6 g/dl) post discharge
nutritional: changes in weight and mid-upper arm circumference (MUAC) at 90 days and 180 days
anti-infection: changes in inflammatory markers (C-reactive protein (CRP) , procalcitonin), incidence of bacterial infections and malaria at 28 days, 90 days and 180 days
solicited adverse events: suspected transfusion reactions: febrile reactions, TRALI (Transfusion Related Acute Lung Injury) (any grade); grade 3–4 toxicity of cotrimoxazole, MVMM or standard iron/folate
serious adverse events
costs and cost-effectiveness

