#### Safety and adverse event reporting

The symptom checklist used at each visit will explicitly prompt for symptoms relating to possible drug toxicities. Additional safety blood tests or investigations may be performed to investigate symptoms or monitor emergent laboratory test abnormalities as clinically indicated. Serious, solicited and grade 3 or 4 adverse events will be reported on the CRF. Adverse events (clinical and laboratory) will be graded according to toxicity/severity grading.

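### The grade 3–4 safety outcome for the post-discharge randomisations depends on an unblinded doctor's attribution, and the rule for recording these events conflicts between sections

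*Protocol article*

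**What the plan says.** Four parts of the protocol article bear on which grade 3–4 events are counted.

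- **Outcomes, Table 3.** Under solicited adverse events, the secondary outcomes include "grade 3–4 toxicity of cotrimoxazole, MVMM or standard iron/folate". This is one pooled line, defined by what caused the event.
- **Follow-up.** At clinic visits after discharge, "grade 3 or 4 adverse events related to nutritional and antibiotic interventions will be documented by a doctor". The same doctor grades the event and judges its cause, the record "including severity and likely relationship of any adverse events to trial interventions".
- **Safety and adverse event reporting.** "Serious, solicited and grade 3 or 4 adverse events will be reported on the CRF". No condition on relatedness is stated. A symptom checklist at each visit prompts for possible drug toxicities.
- **Statistical analysis.** Adverse events are tabulated by body system and randomised arm, and the number per participant is compared by Fisher's exact test. No relatedness filter is stated.

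On blinding, the design section says "All randomisations will be open". The R3 control is no prophylaxis, with no placebo. Methods of reducing bias sets up an Endpoint Review Committee (ERC) blinded to allocation. Its relatedness task covers each trial treatment, judged as if the child were receiving it, and is worded: "The ERC will adjudicate on causes of death and whether fatal and non-fatal SAEs were unlikely, possibly/probably or uncertainly related to each of the randomised" […].

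**The concern.** A doctor who knows that a child is on no prophylaxis cannot ordinarily call a non-serious grade 3 event cotrimoxazole toxicity. The same event in a child on cotrimoxazole can be called that. If relatedness decides what is recorded or counted, the two R3 arms are ascertained differently even when the drug does nothing. Background illness, which is common after severe anaemia, could then appear as drug harm. A count of attributed events also cannot show non-serious events that an intervention prevents.

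The collection rule matters more than the outcome label. If sites follow the Follow-up wording, non-serious events judged unrelated may never reach the database, and no later analysis can recover them.

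**Working it through.** The article gives no figure for this outcome, so there is none to reproduce. The check has two parts.

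**1. The passages side by side**

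| Place | Which grade 3–4 events | Relatedness condition |
|---|---|---|
| Outcomes, Table 3 | toxicity of a named product | yes |
| Follow-up | documented by the visit doctor | yes |
| Safety and adverse event reporting | reported on the CRF | none stated |
| Statistical analysis | adverse events compared by arm | none stated |

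The first two rows filter by cause and the last two do not. The fourth row depends on whichever collection rule sites apply.

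Three further facts set the limits:

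- The Table 3 line also covers MVMM and iron/folate, and every child is allocated one of these under R2. R3 controls can therefore contribute to the pooled line. Only its cotrimoxazole component is nearly confined to one arm.
- Some R3 controls receive cotrimoxazole under guidelines. The article expects children in whom it is mandated or contraindicated to be fewer than 5 %, so 5 % is an upper bound for controls on the drug.
- The ERC's relatedness task names serious events only. For those, judging as if the child received the product lets control-arm events count.

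**2. How large the asymmetry could be (assumed rates)**

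From the article: 3954 children allocated 1:1 in R3, so 3954 / 2 = 1977 per arm.

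Assumed, because the article gives neither:

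- r, the background risk of a grade 3–4 event, equal in both arms (no drug effect).
- a, the share of these events attributed to cotrimoxazole in children known to receive it.

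Expected attributed events are 1977 × r × a in the cotrimoxazole arm and 1977 × r × a × e in control, where e is the share of controls on cotrimoxazole (0 or 0.05).

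With none in control, two-sided Fisher p is 0.062 for 5 v 0 and 0.031 for 6 v 0. For e = 0 the chance of p < 0.05 is therefore P(X ≥ 6), with X ~ Binomial(1977, r × a). For e = 0.05 the same test is summed over both binomial counts.

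| r | a | Expected, cotrimoxazole arm | Expected, control (e = 0.05) | Chance of p < 0.05, e = 0 | e = 0.05 |
|---|---|---|---|---|---|
| 1 % | 10 % | 2.0 | 0.1 | 1.6 % | 1.4 % |
| 1 % | 25 % | 4.9 | 0.2 | 37 % | 32 % |
| 2 % | 10 % | 4.0 | 0.2 | 21 % | 18 % |
| 2 % | 25 % | 9.9 | 0.5 | 93 % | 84 % |
| 5 % | 10 % | 9.9 | 0.5 | 93 % | 84 % |
| 10 % | 10 % | 19.8 | 1.0 | about 100 % | about 100 % |

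Counting all events regardless of attribution gives equal expected numbers under the same assumptions: 1977 × 1 % ≈ 20 v 20, and 1977 × 10 % ≈ 198 v 198.

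**The case against.** The strongest reply is that the article already contains what is needed. The safety section states an unfiltered reporting rule, and the statistical section compares adverse events by arm without a filter. Serious adverse events, readmission, bacterial infection and malaria are separate outcomes that do not depend on attribution. The Follow-up section asks for the relationship of any adverse event, which makes little sense if only related events are recorded. Its wording may simply name the solicited event types, prompted in every child by the checklist. The bias section also says, in general terms, that other clinical secondary endpoints are adjudicated blind. Finally, a condensed article may leave CRF instructions to documents not shown.

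Much of this stands, and it limits the point. It does not remove it, because the two recording rules are both printed and not reconciled, and the outcome itself is worded by attribution. Blinded review cannot restore events that were never recorded.

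A reader might draw stronger conclusions that the article does not support:

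- **That the whole Table 3 line can be non-zero only in the cotrimoxazole arm.** It pools products given in both R3 arms.
- **That non-serious events certainly escape blinded review.** The general statement could include them and the specific task does not, so the article is unclear.
- **That the same fault affects transfusion versus no transfusion.** The withdrawal section says that severe allergic reaction or TRALI "is included as a secondary endpoint and is relevant only to children receiving transfusion". These are by definition events of transfused children, controls who are later transfused can have them, and the sentence does not concern fever or general respiratory deterioration.

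**Conclusion.** The point holds in a limited form. Table 3 and the Follow-up section tie the grade 3–4 outcome to attribution by an unblinded doctor, and this conflicts with the reporting rule in the safety section. If the filter is applied, it also undermines the planned comparison by arm. For non-serious events, the cotrimoxazole component would be ascertained almost only in the cotrimoxazole arm, and it is unclear whether the ERC reviews these events.

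The size cannot be fixed from the article. Under no drug effect, the chance of a nominally significant difference from attribution alone runs from 1 to 2 % to nearly 100 %, depending on assumed background risk and attribution share. Those figures apply only if attributed cotrimoxazole events are what is compared, and 0.05 is an illustrative threshold. No single scenario should be read as a prediction.

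The outcome is secondary, and the mortality primary outcome is unaffected. The change is still worth making because it removes an avoidable bias at little cost.

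**What to change.** 1. In Follow-up, delete the relatedness condition so that all grade 3 or 4 events are documented in every arm, in line with the safety reporting section.
2. In Table 3, define the R2/R3 safety outcome as all grade 3–4 adverse events regardless of attribution, compared by randomised arm as the statistical section already provides.
3. Keep investigator-attributed toxicity of each product as a descriptive tabulation.
4. In Methods of reducing bias, state whether the ERC reviews non-serious grade 3–4 events.

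The cost is a change of wording and one CRF instruction. Background events will be counted in both arms, which adds some noise and data entry. The article reports enrolment as ongoing, with the 1000th of 3954 children (about 25 %) recruited in June 2015. The sponsor should check which rule the CRF has applied so far and report any change of rule with the results.
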